### Withdrawal

At all stages it will be made clear to the parents that they are free to withdraw their infant from the trial at any time, without the need to provide explanation. If parents choose to withdraw, they will be asked for permission to complete data collection and/or follow-up.

The attending clinician may also withdraw the infant from the allocated treatment if they consider this to be in the best interest of the infant’s health and well-being.

### Data collection before discharge

All outcome data are routinely recorded clinical items that can be obtained from the clinical notes or local microbiological laboratory records. No additional blood or tissue samples are required for this trial. Clinical information will be collected using specially created data collection forms.

### Data collection after discharge

A parent questionnaire will assess neurodevelopmental outcomes and health care costs when the infant is 24 months of age (corrected for prematurity).

### Data collection and processing

Data will be processed using validated data management systems to ensure consistency, viability and quality of data. It will be stored in line with the Data Protection Act 1998.

### Safety reporting

Adverse events are defined as serious if they:Result in deathAre life-threateningRequire inpatient hospitalisation or prolongation of existing hospitalisationResult in persistent or significant disability/incapacity, orAre a congenital anomaly/birth defect

The term “life-threatening” refers to an event in which the child was at risk of death at the time of the event; it does not refer to an event which hypothetically might have caused death if it were more severe. SAEs are to be reported from randomisation until discharged home.

Safety reporting will be carried out in accordance with the NPEU Clinical Trials Unit standard operating procedures and clinical regulations.

### Sample size and power

The primary comparison will be the difference in the proportion of infants surviving without moderate or severe disability at 24 months of age corrected for prematurity. Based on previous trials, it is estimated that 80% of the infants will survive to 2 years, and that 11% of these will have a moderate or severe disability [19]. Hence it is estimated the proportion surviving without moderate or severe disability in the control group receiving the 18 ml/kg/day increment will be 71%. With a total sample size of 2500 and allowing for a response rate of 80%, there will be 90% power to detect an absolute difference of 6.3% (from 71.0% in the control group to 77.3%) in this proportion, with a two-sided 5% significance level.

With the same level of significance, a sample size of 2500 infants will have 90% power to detect an absolute risk difference of 5.4% (from 25.0% in control group to 19.6%) in the incidence of sepsis [20] and an absolute risk difference of 3.5% (from 6.0% in control group to 9.5%) in the incidence of NEC (Bell stage 2 or 3) [21–23].

An inflation factor of 1.12 was applied to the sample size to allow for multiple births, expected to have correlated outcomes, receiving the same allocation. This was based on an estimate of 25% for the proportion of multiple births and an intraclass correlation coefficient of 0.9 for the primary outcome at 2 years, based on a similar outcome in a preterm population [24]. The total number of babies that will be recruited will be 2800.

### Statistical analysis

Demographic factors, clinical characteristics and outcomes will be summarised with counts (percentages) for categorical variables, mean (standard deviation) for Normally distributed continuous variables, or median (interquartile or entire range) for other continuous variables. Infants will be analysed according to allocation regardless of the speed of milk feed increase they actually receive.

The two groups will be compared using generalised estimating equations, adjusting for the minimisation factors to account for the correlation between treatment groups. This method of analysis will also account for the correlation in outcomes between twins and siblings born in a subsequent pregnancy during the trial period. For the primary outcome, an adjusted risk ratio with 95% confidence will be calculated using log binomial regression, or log poisson regression with a robust variance estimator if the binomial model fails to converge [25]. Linear regression will be used for Normally distributed outcomes, quantile regression for skewed continuous variables, and Cox regression for time to event outcomes. Ninety-nine percent confidence intervals will be calculated for all secondary outcomes.

The consistency of the effect of advancing milk feeds across specific subgroups of infants will be assessed using the statistical test of interaction. Pre-specified subgroup analyses include: (i) week of gestation at birth, (ii) birth weight (<10th centile for gestational age versus ≥ 10th centile and (iii) type of milk (breast milk only/formula only/mixed). Subgroup analysis will be performed on the primary outcome, and the incidence of sepsis and NEC.

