### Secondary outcomes

Secondary outcomes to be assessed when infants are discharged home for the first time are:Survival to discharge home.Microbiologically-confirmed or clinically suspected late-onset invasive infection from trial entry to discharge home.NEC (Bell stage 2 or 3) from trial entry to discharge home.Time taken to reach full milk feeds (tolerating 150 ml/kg/day for 3 consecutive days).Growth (change in z score–weight and head circumference for gestational age) from birth to discharge home.Duration of parenteral feeding.Length of time in intensive care.Length of hospital stay to discharge home.

In addition, the separate components of the composite primary outcome at 24 months of age corrected for prematurity will be analysed individually as secondary outcomes. The diagnosis of cerebral palsy by a doctor or other health professional will also be a secondary outcome assessed at this age.

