### Randomisation and allocation

Randomisation will take place at the time the clinician is ready to start increasing the feed volume. This will be performed through a secure website hosted by the NPEU CTU with telephone back-up available 24/7, 365 days a year.

A minimisation algorithm will be used to ensure balance on important prognostic factors: hospital, multiple birth, gestational age ranges, and birth weight <10th centile for gestational age. Multiple births will be given the same allocation.

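### The stated adjustment uses gestation in ranges and birth weight as a 10th-centile flag; finer baseline values already needed elsewhere would recover some precision, mainly for duration outcomes

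*Protocol article*

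**What the plan says.** In the protocol article, the Statistical analysis section compares the groups by generalised estimating equations, "adjusting for the minimisation factors to account for the correlation between treatment groups". It names no other covariate. The Randomisation and allocation section gives the factors as "hospital, multiple birth, gestational age ranges, and birth weight <10th centile for gestational age". It does not give the cut-points of the gestation ranges.

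Finer forms of the same two factors appear elsewhere. The subgroup list in Statistical analysis opens with "i) week of gestation at birth". The Secondary outcomes section includes "Growth (change in z score–weight and head circumference for gestational age) from birth to discharge home", which requires a weight z score at birth.

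The Secondary outcomes section also lists "Length of hospital stay to discharge home", together with time in intensive care, duration of parenteral feeding and time to full feeds. No model is assigned to any of these by name. By outcome type they fall under "quantile regression for skewed continuous variables, and Cox regression for time to event outcomes". On interval width the section says: "Ninety-nine percent confidence intervals will be calculated for all secondary outcomes".

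**The concern.** Gestation at birth is likely to be among the strongest predictors of outcome in these infants, above all for durations in hospital. This is clinical reasoning; the article gives no figure for it. Cutting gestation into ranges, and birth weight for gestation into two classes, leaves the prognostic variation within each class in the error term. Chance differences between the arms within a class then also stay in the estimate as random error.

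At stake is the width of the intervals, not their validity. Duration outcomes already carry 99% intervals, and the Discussion rests part of the case for the trial on shorter stay. Both finer values are fixed before randomisation, so using them introduces no post-randomisation bias and needs no new data.

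**Working it through.** **1. The plan's own figure.** Inputs from Sample size and power: 71.0% against 77.3%, 90% power, two-sided 5%, 80% response, total 2500. With pooled variance and no continuity correction:

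n per arm = [1.960 × √(2 × 0.7415 × 0.2585) + 1.282 × √(0.71 × 0.29 + 0.773 × 0.227)]² / 0.063² = 1013.

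The total is 2026 / 0.8 = 2533, against 2500 stated (1.3% apart). With 1000 analysed per arm, power is 89.6%. Then 2500 × 1.12 = 2800, as stated. The figure reproduces, and it takes no credit for covariate adjustment, so nothing below undermines it.

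**2. Formula for the loss.** On a linear scale, the variance of the treatment effect is proportional to 1 − R². Hence

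variance ratio = (1 − R² with bands and flag) / (1 − R² with continuous gestation and z score),

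and excess interval width = √(variance ratio) − 1. The percentage excess is the same for 95% and 99% intervals.

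**3. Assumed inputs (none is in the article).** 400,000 simulated infants; gestation spread over weeks 23-32 and weighted towards the later weeks; birth-weight z score normal with mean −0.2 and SD 1; the flag set at z below −1.28; linear effects, with 90% of the explained variance due to gestation and 10% to birth weight. Four codings of gestation were tried: one-week bands, two-week bands, three bands (<26, 26-28, 29+) and two bands (<28, ≥28).

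**4. Length-of-stay-type outcome.** Variance ratio, with excess interval width in brackets:

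| Gestation coding, plus flag | R² 0.4 | R² 0.5 | R² 0.6 |
|---|---|---|---|
| One-week | 1.049 (2.4%) | 1.075 (3.7%) | 1.112 (5.4%) |
| Two-week | 1.076 (3.7%) | 1.114 (5.5%) | 1.170 (8.2%) |
| Three bands | 1.151 (7.3%) | 1.228 (10.8%) | 1.338 (15.7%) |
| Two bands | 1.235 (11.1%) | 1.349 (16.2%) | 1.526 (23.5%) |

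Example for two-week bands at R² 0.5: (1 − 0.442) / (1 − 0.499) = 1.114, and √1.114 − 1 = 5.5%. If R² is only 0.2, the excess widths fall to 0.9%, 1.4%, 2.8% and 4.3%.

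With one-week bands, most of the loss comes from the birth-weight flag. At R² 0.4, the bands with the flag reach 0.372, the bands with a continuous z score 0.396, and the fully continuous model 0.402.

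A separate linear simulation assumed 7 days of stay per week of gestation, 3 days per SD of z score, residual SD 12-20 days and 2240 infants. It gave variance ratios of 1.06-1.17 for two-week ranges and 1.10-1.28 for three-week ranges. As widths these are √1.06 − 1 = 3.0% to √1.17 − 1 = 8.2%, and √1.10 − 1 = 4.9% to √1.28 − 1 = 13.1%.

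**5. Median regression.** With a skewed stay, the same slopes, residual SD 12/15/20 and 400 replicates (so with appreciable Monte Carlo noise), the variance ratios were 1.22/1.04/0.99 for two-week bands, 1.46/1.27/1.05 for three-week bands and 1.01-1.03 for one-week bands. The gain can carry over to quantile regression, but it vanishes when the bands are narrow or the residual SD is large.

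**6. Primary outcome.** Assumed log-odds slopes are 0.2, 0.3 and 0.4 per week and 0.2 per SD of z score, giving R² of 0.050, 0.100 and 0.161. If the banded analysis has 90% power, power with finer terms = Φ(3.242 × √ratio − 1.960).

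| Gestation coding, plus flag | Variance ratio, three slopes | Power, three slopes |
|---|---|---|
| One-week | 1.005 / 1.007 / 1.007 | 90.1 / 90.2 / 90.2% |
| Two-week | 1.007 / 1.011 / 1.014 | 90.2 / 90.3 / 90.4% |
| Three bands | 1.012 / 1.020 / 1.030 | 90.3 / 90.6 / 90.8% |
| Two bands | 1.017 / 1.034 / 1.051 | 90.5 / 90.9 / 91.4% |

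The loss is at most 3% of variance unless gestation is cut only once. The gain of 1.4 points needs both that single cut and the steepest slope.

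**The case against.** The strongest reply is that the article names which factors to adjust for, not how they are coded. The ranges belong to the allocation algorithm, and entering gestation by week would still be adjusting for gestation. A statistical analysis plan, not shown here, may do exactly that. An interaction test by week of gestation would also normally carry week as a main effect. This stands in part: a reader might infer that every model uses only the coarse forms, and the text does not say so. It remains true that the adjustment set is stated, that its listed members are coarse, and that this is the direct reading.

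A reader might also infer from the linear figures that the planned coding costs the equivalent of 6-28% more infants for length of stay. The documents do not support that. Those figures leave out one-week bands, for which the loss is small, and the slopes and residual SDs are assumed. The plan also points to quantile or Cox regression for durations. In a Cox model, adding a prognostic covariate changes the conditional hazard ratio and does not simply narrow the interval. That length of stay gains most is plausible, but no figure in the article shows it.

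Nor can the point be extended to costs. The Economic data collection section describes bootstrapped intervals around mean costs and no covariate-adjusted model.

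Two further replies stand. Adjusting for the minimisation factors respects the design, and chance imbalance within a range is random error already reflected in the interval, not bias. Adding terms also has a price: the plan already foresees that the log-binomial model may not converge, and smooth terms alongside about 30 hospitals may make that more frequent.

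**Conclusion.** The point holds as an optional efficiency improvement. On the direct reading, the planned adjustment is coarser than the baseline data allow, and some precision is given up. For the primary outcome this hardly matters: 0.5-3% of variance in all scenarios but the widest banding, and 5.1% (1.4 power points) in the most extreme one. For durations driven by gestation, the excess interval width on a linear scale runs from about 2% (one-week bands, R² 0.4) to about 24% (two bands, R² 0.6).

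These sizes rest on assumed R², an assumed gestation distribution and assumed band widths. None can be fixed from the article, and the gain under quantile or Cox regression may be larger, smaller or absent. The planned analysis is valid and the sample size is unaffected. No claim is made about the cost intervals.

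**What to change.** In Statistical analysis, keep hospital and multiple birth as adjustment factors. Prespecify gestational age at birth as a continuous smooth term (for example weeks and days, with a quadratic or spline) and birth-weight z score for gestational age as a continuous term, in place of or alongside the ranges and the 10th-centile flag, in the outcome models. If a separate analysis plan already codes the factors this way, it is enough to align the wording.

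The cost is a line of text, settled before analysis; it needs no extra infants and no extra data. The one downside is that the log-binomial model may fail to converge more often. The Poisson model with robust variance, which the plan already names, then applies.

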### Nutritional support of preterm infants and speed of increasing milk feeds

Every year in the UK around 8000 infants are born so preterm that they cannot initially be fed milk and therefore require intravenous nutrition. Milk feeding is gradually increased as the immature gut begins to tolerate milk and intravenous nutrition is correspondingly reduced, but there are few data determining how quickly this is best achieved [6].

One of the most serious complications of intravenous feeding is late-onset sepsis, which occurs in 27% of infants born weighing less than 1500 g at birth or under 29 weeks’ gestation [6]. Late-onset sepsis is known to cause poor long-term cognitive outcomes, liver damage and also sudden death from cardiac problems resulting from misplaced catheters [7–9]. One of the most common late-onset infections is ‘catheter-related bloodstream infection’; the risk of bloodstream infection being directly related to the time the catheter is indwelling in the bloodstream [10–12].

The more rapid advancement of enteral feeds described in this study will, in principle, reduce exposure to intravenous nutrition by causing infants to reach full milk feeds (tolerating 150 ml/kg/day for 3 consecutive days) about 4 days earlier than the slower advancement. Reducing exposure by this amount could reduce the number of infections by between 5 and 15 cases per 250 infants, which is an absolute risk reduction of 4%. This is possibly an underestimate of the reduction as infection risk increases with the length of time a catheter is in place [13, 14].

However, faster increases in milk feed volumes may increase the likelihood of NEC which, as well as being potentially fatal, may provoke intolerance of feeds or gut dysfunction that could result in longer times to achieve full feeds rather than shorter. Survivors of NEC also have significantly worse long-term outcomes across multiple developmental domains than those unaffected [5, 15].

Therefore, while emerging data suggest better health outcomes may be achieved with faster feeding increments, there are possible disadvantages and a randomised controlled trial is required to support a change in clinical practice [6].

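### The 90% power given for sepsis and NEC is at the 5% level, but the plan reports both with 99% confidence intervals, for which the corresponding power is about 75% (at most about 81%)

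*Protocol article*

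**What the plan says.** Under Secondary outcomes, the protocol article lists late-onset invasive infection and NEC (Bell stage 2 or 3), each counted from trial entry to discharge home.

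Under Sample size and power, the primary outcome is powered "with a two-sided 5% significance level". The next paragraph carries that level over to two secondary outcomes: "With the same level of significance, a sample size of 2500 infants will have 90% power". For infection, the target it names is this: "absolute risk difference of 5.4% (from 25.0% in control group to 19.6%) in the incidence of sepsis". For the bowel outcome, the corresponding target reads: "an absolute risk difference of 3.5% (from 6.0% in control group to 9.5%) in the incidence of NEC". No other secondary outcome has a power statement.

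Under Statistical analysis, the primary outcome gets a risk ratio with a 95% interval. For the rest, "Ninety-nine percent confidence intervals will be calculated for all secondary outcomes". The word used is all, and neither sepsis nor NEC is set apart.

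**The concern.** The power statement and the analysis use different levels for the same two outcomes. A 99% interval excludes no effect exactly when the matching two-sided test has p below 0.01, so 90% power at 5% does not describe how often the planned interval will exclude no effect when the stated difference is real.

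These two outcomes carry much of the trial's rationale. The Background presents fewer infections as the expected gain from faster feeding and NEC as the possible harm. Both are named in the secondary objectives, and sepsis avoided is also an outcome in the main economic analysis. The discrepancy matters most for NEC. A reader who sees a 99% interval that includes no effect, and who has read the 90% figure, would put the chance of missing a true 3.5-point rise at 10%. With an effective 2500 infants it is about 24%. Leaving two levels side by side also leaves the choice of criterion open until the results are known.

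**Working it through.** **Inputs**
- Sepsis 25.0% versus 19.6%; NEC 6.0% versus 9.5%; 2500 infants; two-sided 5% (Sample size and power).
- Inflation factor 1.12 for multiple births: 2500 × 1.12 = 2800 recruited, so 2500 is the effective number if that factor applies (same section).
- 99% intervals for secondary outcomes (Statistical analysis), i.e. two-sided 1%.
- Assumptions: 1:1 allocation, so 1250 per arm (the ratio is not stated, but this reproduces the stated power); no loss of data for sepsis and NEC, since the 80% response rate is applied only to the 24-month outcome.

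**Formula** (two proportions, normal approximation)

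Power = Φ[(d − z·s0)/s1], where d is the absolute difference, s0 = √(2·p̄(1 − p̄)/n), s1 = √((p1(1 − p1) + p2(1 − p2))/n), p̄ is the mean of p1 and p2, n is the number per arm, and z is 1.960 at 5% or 2.576 at 1%.

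**Step 1: reproduce the stated 90%** (n = 1250, z = 1.960)
- Sepsis: d = 0.054, p̄ = 0.223, s0 = 0.01665, s1 = 0.01661. (0.054 − 1.960 × 0.01665)/0.01661 = 1.286, power 90.1%.
- NEC: d = 0.035, p̄ = 0.0775, s0 = 0.01070, s1 = 0.01067. (0.035 − 1.960 × 0.01070)/0.01067 = 1.315, power 90.6%.

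The stated figure is right at the stated level.

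**Step 2: the level that matches a 99% interval** (n = 1250, z = 2.576)
- Sepsis: (0.054 − 2.576 × 0.01665)/0.01661 = 0.669, power 74.8%.
- NEC: (0.035 − 2.576 × 0.01070)/0.01067 = 0.698, power 75.7%. The chance of missing the rise is 100 − 75.7 = 24.3%.

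The method hardly matters. With unpooled variance the 1% figures are 75.0% and 75.9%; on the log risk ratio scale, which is closer to the planned analysis, they are 74.3% and 74.6%.

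**Step 3: sensitivity to the multiple-birth adjustment**

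The 1.12 factor rests on an intraclass correlation of 0.9 for the primary outcome. None is given for sepsis or NEC. At the favourable extreme, with no correlation within multiples, all 2800 infants count in full (n = 1400):

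| Outcome | 5%, n = 1250 | 1%, n = 1250 | 1%, n = 1400 |
|---|---|---|---|
| Sepsis | 90.1% | 74.8% | 80.5% |
| NEC | 90.6% | 75.7% | 81.3% |

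**Step 4: what 90% power at 1% would correspond to**

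Solving the same formula for d at n = 1250 gives 6.4 points for sepsis (25.0% to 18.6%) and 4.2 points for NEC (6.0% to 10.2%). Detecting the stated differences instead would need an effective total of 3532 (sepsis) or 3470 (NEC), before any inflation for multiple births.

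**The case against.** The best case for the plan is that it says only that 99% intervals will be calculated. It never states a 1% test for any outcome, and the one significance level it attaches to sepsis and NEC is 5%. Wider intervals can be a cautious reporting convention for many secondary outcomes, compatible with a 5% power statement, and how they are to be read may be settled in a fuller document that is not shown. The first part of this stands: treating the 99% interval as a 1% criterion is an inference, and the point has to be put conditionally. It does not remove the inconsistency. The interval is the only criterion the article gives for secondary main effects, and the article itself states both levels without reconciling them.

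A second objection is that 75% assumes the primary outcome's multiple-birth adjustment carries over to sepsis and NEC. That also stands, and is why a range is given. The top of the range is still well below 90%.

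Some stronger readings are tempting but not supported:
- That the 90% was miscalculated. It was not; it reproduces at 5%.
- That 99% intervals are a poor choice. They are a reasonable guard against multiplicity, and the point is only that the power statement does not go with them.
- That power is worse still because the Background mentions "which is an absolute risk reduction of 4" percent for infection. The same sentence gives 5 to 15 fewer cases per 250 infants, which is 2 to 6 points (5/250 and 15/250) and contains the 5.4-point target. The next sentence says the reduction may be an underestimate. The choice of target difference is in any case a separate matter from the mismatch of levels.

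**Conclusion.** The point holds as an inconsistency between the power statement and the analysis. The 90% for sepsis and NEC belongs to a two-sided 5% criterion. If the planned 99% intervals are what an effect is judged by, power for the stated differences is about 75% with an effective 2500 infants and at most about 81% with all 2800 counted in full. This rests on 1:1 allocation, complete in-hospital data and the rates in the article.

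It should be corrected, but it is not a fundamental fault. The recruitment target and the primary outcome's power and 95% interval are untouched. A reader might infer that the trial is too small; the documents do not support that, since the sample size is set by the primary outcome and these are supporting statements for two secondary outcomes.

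**What to change.** State the level at which sepsis and NEC will be interpreted, and make the two sections agree, before results are seen. Either of these would do:

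1. Keep 99% intervals throughout and restate the power for these two outcomes at two-sided 1%: about 75% for 5.4 and 3.5 points (range 75–81%, depending on correlation within multiple births), with 90% power for about 6.4 points (sepsis) and 4.2 points (NEC) at an effective 2500.
2. If 5% is intended for the two powered secondary outcomes, say so, report them with 95% intervals, and keep 99% for the remaining secondary outcomes. The stated 90% then stands.

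Both are changes of wording and need no extra infants. The first makes the stated power less favourable; the second gives up the stricter multiplicity guard for two outcomes.
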